## Abstract

**Background:**

Electroconvulsive therapy (ECT) is the most effective treatment for severe depression, but its use is impeded by its cognitive side effects. Novel treatments that can counteract these side effects may therefore improve current treatment strategies for depression. The present randomized trial investigates (1) whether short-term add-on treatment with erythropoietin (EPO) can reduce the cognitive side -effects of ECT and (2) whether such effects are long-lasting. Further, structural and functional magnetic resonance imaging (MRI) will be used to explore the neural underpinnings of such beneficial effects of EPO. Finally, the trial examines whether potential protective effects of EPO on cognition are accompanied by changes in markers of oxidative stress, inflammation, and neuroplasticity.

**Methods/design:**

The trial has a double-blind, randomized, placebo-controlled, parallel group design. Patients with unipolar or bipolar disorder with current moderate to severe depression referred to ECT (*N* = 52) are randomized to receive four high-dose infusions of EPO (40,000 IU/ml) or placebo (saline). The first EPO/saline infusion is administered within 24 h before the first ECT. The following three infusions are administered at weekly intervals immediately after ECT sessions 1, 4, and 7. Cognition assessments are conducted at baseline, after the final EPO/saline infusion (3 days after eight ECT sessions), and at a 3 months follow-up after ECT treatment completion. The neuronal substrates for potential cognitive benefits of EPO are investigated with structural and functional MRI after the final EPO/saline infusion. The primary outcome is change from baseline to after EPO treatment (3 days after eight ECT sessions) in a cognitive composite score spanning attention, psychomotor speed, and executive functions. With a sample size of *N* = 52 (*n* = 26 per group), we have ≥ 80% power to detect a clinically relevant between-group difference in the primary outcome measure at an alpha level of 5% (two-sided test). Behavioral, mood, and blood-biomarker data will be analyzed using repeated measures analysis of covariance. Functional MRI data will be preprocessed and analyzed using the FMRIB Software Library.

**Discussion:**

If EPO is found to reduce the cognitive side effects of ECT, this could have important implications for future treatment strategies for depression and for the scientific understanding of the neurobiological etiology of cognitive dysfunction in patients treated with ECT.

**Trial registration:**

ClinicalTrials.gov, NCT03339596. Registered on 10 November 2017.

**Electronic supplementary material:**

The online version of this article (10.1186/s13063-018-2627-2) contains supplementary material, which is available to authorized users.

## Background

Electroconvulsive therapy (ECT) is an effective, fast-acting, and safe treatment for severe depression [1], but it is associated with troublesome cognitive side effects across episodic memory, attention, and executive functions that persist for weeks [2, 3] to months after treatment completion [4, 5]. Such cognitive side effects of ECT are the greatest impediment to its prescription for depression, making it reserved for only the most severely ill patients [6]. Therefore, novel treatments that counteract these side effects have the potential to improve current treatment strategies by allowing a greater number of severely ill patients to get earlier and more effective treatment with fewer cognitive side effects. However, research efforts into identification of methods to attenuate the cognitive side effects of ECT treatment without hampering its clinical efficacy have thus far been unsuccessful [7].

Erythropoietin (EPO) is a promising treatment for cognitive dysfunction in mood disorders [8, 9] and for counteracting ECT-induced cognitive side effects. EPO is not only produced systematically in the kidneys, but is also produced in the brain, where it mediates neuroprotection and development, modulates oxidative stress and inflammation [10], and plays a key role in cognitive functioning [11, 12]. Systemically administered EPO crosses the blood-brain barrier and has been shown in preclinical studies to mediate neuroprotection and neuroplasticity and to enhance cognitive functions when given in high doses (≥ 500 IU/kg body weight) [13, 14]. Randomized controlled clinical studies suggest that 8–12 weeks of systemically administered high-dose (40,000–48,000 IU) EPO improves attention, memory, and executive functions in patients with treatment-resistant depression (TRD) [9], bipolar disorder (BD) [8], multiple sclerosis [15], or schizophrenia [16]. The cognitive benefits of EPO treatment seem to result from direct neurobiological actions rather than non-specific changes in red blood cells. For example, randomized placebo-controlled functional magnetic resonance imaging (fMRI) studies by our group [17, 18] showed that a single high dose (40,000 IU) of EPO vs. placebo enhanced memory-relevant prefrontal and hippocampal activity in healthy and depressed individuals without affecting red blood cells. Consistent with this, our subsequent randomized, placebo-controlled trials revealed that eight weekly infusions of high-dose (40,000 IU) EPO vs. saline had mood-independent beneficial effects on cognitive function in patients with TRD (*N* = 40) and BD in remission (*N* = 44) [8, 9]. These cognitive benefits were accompanied by EPO-associated increase in neural activity within the frontal and the parietal lobes during strategic encoding and working memory tests [8, 9, 19]. Notably, EPO-related memory improvement in these patients was associated with reversal of hippocampal (cornu ammonis 1–3) and subiculum volume loss [20], which is interesting in light of ECT induction of hippocampal volume increase (see, e.g., [21]). Importantly, these brain changes were independent of changes in mood and lasted long term beyond red blood cell normalization. Several neurobiological actions may underlie these beneficial cognitive effects of EPO treatment, including activation of anti-inflammatory, anti-apoptotic, and antioxidant signaling pathways [14, 22, 23] and growth of dendrites, maturation of neural progenitor cells, and upregulation of brain-derived neurotrophic factor (BDNF) [24, 25]. Taken together, preliminary findings highlight EPO as a candidate treatment for ECT-induced cognitive deficits in mood disorders. This trial extends our previous work by investigating for the first time whether adjunctive EPO treatment can counteract the cognitive side effects of ECT.

### Aims and hypotheses

The present trial aims to investigate whether one primer infusion of EPO/saline before ECT followed by three weekly EPO/saline infusions during the course of ECT counteracts cognitive side effects in patients receiving ECT. Furthermore, we aim to investigate the neuronal underpinnings of such potential effects of EPO with structural and functional magnetic resonance imaging (MRI) and the role of oxidative, inflammatory, and neuroendocrinological systems with blood and urine tests.

We hypothesize that EPO treatment will (1) counteract ECT-induced decline in cognition (primary endpoint), which will be accompanied by (2) increased subregional hippocampal volume, (3) greater memory-related hippocampal activation and reinforcement of dorsolateral prefrontal activity during memory encoding and working memory, and (4) changes in peripheral markers of inflammation, oxidative stress, and neuroplasticity. Given preliminary evidence for the beneficial effects of EPO on depression-relevant outcomes [8, 13], a secondary hypothesis is that add-on EPO treatment will produce greater, more sustained mood improvement than ECT treatment alone.

## Methods/design

### Participants and screening

A total of 52 patients with major depression (MDD) or BD scheduled for ECT treatment will be recruited from Psychiatric Centers in The Mental Health Services in the Capital Region of Denmark. Half of the participants will be randomized to receive active EPO treatment (*n* = 26), while the other half will receive a placebo (saline) (*n* = 26).

Prior to enrollment, patients will be screened with the *Mini International Neuropsychiatric Interview* (MINI) [26] to confirm their International Statistical Classification of Diseases and Related Health Problems (ICD-10) diagnosis. Eligible patients have a diagnosis of MDD, unipolar disorder (UD), or BD with current moderate to severe depressive episode symptoms, a Hamilton Depression Rating Scale, 17 items (HDRS-17) score ≥ 17 [27], are 18–70 years of age, have fluent Danish skills, and are able to provide informed consent. Exclusion criteria are treatment under involuntary measures, previous ECT within the last 3 months, other neuropsychiatric conditions, alcohol or substance misuse disorder, or recent suicide attempts. To ensure the safety of the EPO treatment, patients are also excluded if they have a significant medical condition (including diabetes, renal failure, heart disease, epilepsy, untreated/insufficiently treated hypertension, malignancies, or thromboses), are pregnant, use contraceptive medication, or have a family history of thromboses or epilepsy, similar to our previous studies [28]. Pregnancy tests are mandatory for and will be performed on female patients in their fertile age before their inclusion in the trial. Patients will also be excluded if they are overweight (body mass index (BMI) > 30) or have a body weight < 45/> 95 kg. Blood screening and physical examinations are undertaken at baseline and weekly during the 3-week EPO treatment period to ensure patient safety. These exclusion criteria and weekly safety monitoring prevented serious adverse events in our previous EPO trials [8, 9, 28]. Written informed consent is obtained by one of the named authors before inclusion. The procedures are in accordance with the ethical standards of the Danish Research Ethics Committee for the Capital Region.

### Setting

Patients will be randomized to receive a total of four intravenous infusions of either recombinant human EPO (40,000 IU/ml; Epoetin alfa; Eprex, Janssen-Cilag) or a placebo (1 ml NaCl) diluted with 100 ml saline (0.9% NaCl) that is administered over 15 min. The first infusion is given within 24 h before the first ECT, and the following three infusions are administered immediately after ECT at weekly intervals (after ECT sessions 1, 4, and 7). The treatment and all the outcome assessments will take place at Psychiatric Center Copenhagen, Psychiatric Center Glostrup, or Psychiatric Center Amager. Functional MRI is conducted at Copenhagen University Hospital, Rigshospitalet. Participants will be transported to and back from Copenhagen University Hospital in a safe setting by two members of our research team. Furthermore, to ensure the quality and the reliability of the blood test results, all the blood samples will be analyzed at the same laboratory, also at the Copenhagen University Hospital, Rigshospitalet.

### Study design and procedures

The trial has a randomized, double-blinded, placebo-controlled, parallel group design. The study design and procedures are summarized in Fig. 1. The Standard Protocol Items: Recommendations for Interventional Trials (SPIRIT) checklist is provided in Additional file 1. Cognitive functions, mood symptoms, and blood and urine markers of inflammation, oxidative stress, and neuroplasticity will be assessed three times during the trial. The first time will be at baseline, the second time post-EPO treatment 3 days after ECT session 8 (patients skip one ECT session day after eight ECTs to minimize the confounding effects of *acute* side effects of ECT due to anesthesia, etc.), and the third time at a 3 months follow-up after ECT completion. In addition, the neuronal substrates for potential effects of EPO on cognition are investigated with structural and fMRI after eight ECT sessions (i.e., after three weekly EPO or saline infusions). The rationale for assessing cognition and neuronal activity after eight ECTs is to ensure participation of almost all patients, given our experience that > 95% of patients need eight or more ECTs (unpublished observations from [29]) post-treatment. EPO/saline will be administered when patients wake up following ECT. The EPO doses are identical to those found to modulate neural and cognitive function with short-term administration [17] and to improve cognition with long-term treatment [8, 9, 16, 30]. Concomitant medication is kept stable for the duration of the study, unless the individual patient’s psychiatrist deems it necessary to change medication.

**Fig. 1 Fig1:**
[figure not shown]
Schedule of enrollment, interventions, and assessments. Abbreviations: *AMI-SF* Columbia University Autobiographical Memory Interview-Short Form, *RAVLT* Rey Auditory Verbal Learning Test, *TMT-B* Trail Making Test Part B, *WAIS-III LNS* Wechsler Adult Intelligence Scale Version III Letter-Number Sequencing, *RBANS Coding* Repeatable Battery for the Assessment of Neuropsychological Status Coding, *RVP* Rapid Visual Processing (*CANTAB* Cambridge Cognition Ltd.), *HDRS-17* Hamilton Depression Rating Scale, 17-item version, *BDI-21* Beck Depression Inventory, 21 items, *COBRA* Cognitive Complaints in Bipolar Disorder Rating Assessment, *CTQ* Childhood Trauma Questionnaire

EPO is kept at 2–8 °C during transport and storage to minimize the risk of damaging the medication and potential side effects. EPO will be dissolved in 100 ml saline and administered intravenously over 15 min. Patients will stay at the clinic for observation for at least 30 min after each infusion in case of acute severe adverse events. In cases of significantly increased hematocrit (men > 50%, women > 48%) at two consecutive blood test measurements within the same week, bloodletting (450 ml) will be performed on a weekly basis with no cessation of treatment until hematocrit values are normalized. In the case of a significant increase in thrombocytes (> 400 billion/L) or a drop in reticulocytes (< 1‰), two repeated controls will be performed in the following week. If the values stay abnormal, the patient will be withdrawn from further study participation and monitored with weekly medical examinations and blood samples until he or she is stabilized. If deemed necessary by the medic responsible for patient safety, the patient might be hospitalized for observation. Procedures for breaking randomization codes are established in the case of serious adverse events potentially or directly related to the medical intervention. These procedures will be followed if knowledge of the patient’s medical treatment will have implications for treatment of the observed serious adverse events. The principal investigator or any medical doctor responsible for the patient is able to decide whether to break emergency envelopes for potentially affected patients.

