### Statistical analyses

The statistical significance threshold is considered to be *p* < 0.05 (two-tailed). Behavioral, mood, and biomarker data will be analyzed using a mixed models design and an intention-to-treat (ITT) approach. Structural and functional imaging data will be collected using a 3 T MR scanner operating at Copenhagen University Hospital, Rigshospitalet. Resting state and task-related fMRI data will be preprocessed and analyzed using the FMRIB Expert Analysis Tool (FEAT) and the ‘randomize’ algorithm integrated in the FMRIB Software Library (FSL), www.fmrib.ox.ac.uk/fsl. We will adjust for potential differences in demographical and clinical parameters at baseline. All statistical analyses will be run using the *Statistical Package for Social Sciences* (SPSS, version 23, IBM Corporation, Armonk, NY).

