### Safety procedures and monitoring

EPO is commonly used in the treatment of anemia and has a good safety profile when carefully monitored. Nevertheless, hematopoietic effects of repeated EPO administration are associated with increased risk of hypertension and blood clotting [51]. For instance, EPO has been associated with increased mortality in severely ill stroke patients with a previous history of thromboembolic disease, including patients given thrombolytic treatment [52, 53]. To ensure patient safety in this trial, we have extensive exclusion criteria to exclude participants at increased risk of thromboembolic events. There is also some concern that EPO may increase the risk of tumor growth, although the evidence for this is unclear [54]. The rare condition called pure red cell aplasia (PRCA) has been detected with subcutaneous injections and poor packaging of the EPO medicine. However, its incidence rate has fallen to 0.3/100,000 patient years [55–57]. Given thorough adherence to the exclusion criteria and the weekly safety monitoring, we evaluate the risk of such severe side effects and adverse events of EPO treatment in this trial to be extremely low. Since reticulocyte counts constitute the first indicator of PRCA, these counts will be carefully monitored. We observed no serious adverse events of 8 weekly EPO infusions in the proposed dose and administration form in our previous studies including patients with mood disorders [8, 9]. EPO-related hematocrit levels increased to an extent that necessitated bloodletting in 5 (14%) of the 35 EPO-treated patients in weeks 3–8 (only 1 in week 3), which corresponds to observations by Ehrenreich et al. [15, 16]. We discontinued EPO treatment in six patients (17%) after 5–7 weeks due to thrombocyte level increase. Since we give only 3 weeks of EPO treatment in the present study (four doses), we do not expect such side effects. Accordingly, safety monitoring involves thorough medical examinations, blood pressure measures, blood sampling, electrocardiography (ECG), and the measurement of additional safety parameters at baseline, weekly during the study, and at 3 weeks after EPO/placebo treatment completion. Patients will be informed of all potential adverse effects before randomization and told that iron supplements (which increase hematocrit levels) are prohibited. Although the risk of potential thrombosis or suspected PRCA is low, participants will be given a pocketsize plastic card with instructions about what to do and contact details to medical doctors at the local emergency department in case of these symptoms.

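### Safety withdrawal ends study participation rather than only study medication, and this is not reconciled with the stated intention-to-treat approach

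*Protocol article*

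**What the plan says.** The text after Fig. 1 (Study design and procedures) treats abnormal blood counts in two ways. A raised hematocrit leads to bloodletting "with no cessation of treatment until hematocrit values are normalized". For thrombocytes above 400 billion/L or reticulocytes below 1‰, "two repeated controls will be performed in the following week". The next step reads: "If the values stay abnormal, the patient will be withdrawn from further study participation", with weekly examinations and blood tests continuing until the patient is stable. Nothing there says that cognition or any other outcome is still assessed.

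Under Statistical analyses, behavioral, mood and biomarker data are to be "analyzed using a mixed models design and an intention-to-treat (ITT) approach".

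Safety procedures and monitoring reports the earlier eight-week experience: EPO was stopped for rising thrombocytes in six patients (17%), after 5–7 weeks. The same section does not expect these effects with four doses over three weeks.

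**The concern.** The article has wording for stopping the drug alone and uses it elsewhere, for hematocrit and for the earlier trials. Here it ends participation in the study. Taken literally, a withdrawn patient has no further cognitive assessment, although the same patient is still seen weekly for safety.

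An intention-to-treat comparison is only as good as the outcomes collected after randomisation. If the reason for loss is an effect of the active drug, the loss is related to treatment, and the randomised comparison is weakened in a way that analysis can repair only under assumptions. The sample size also has almost no slack.

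**Working it through.** **Inputs.** 26 patients per arm, difference 0.4, SD of change 0.5, two-sided alpha 5%, power at least 0.8 (Sample size and power calculation). Primary assessment 3 days after ECT session 8 (Study design and procedures). ECT on Mondays, Wednesdays and Fridays (ECT procedures). 6 of 35 EPO patients stopped for thrombocytes after 5–7 weeks, and a safety check 3 weeks after the end of EPO/placebo (Safety procedures and monitoring).

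**1. The plan's own figure.** Two-sample t test with noncentrality 0.4 / (0.5 × √(1/26 + 1/26)) = 2.88 on 50 degrees of freedom: power 0.807. At 25 per arm it is 0.791, so 26 is the smallest group size that reaches 0.8. The normal approximation gives 0.822 at 26 and needs 25 per arm. The stated sample size is reproduced, with essentially no allowance for loss.

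**2. Timing of the primary visit.** Counting from the first ECT as day 0, sessions 1, 4 and 7 fall on days 0, 7 and 14 whichever weekday treatment starts. Session 8 falls on day 16 (Monday or Wednesday start) or day 17 (Friday start). The primary visit is therefore on day 19 or 20. The article does not give the days of the weekly blood tests; I assume they fall on the infusion days.
- Abnormal on day 7: the repeat tests fall before the primary visit on most readings, so that visit can be lost.
- Abnormal on day 14: if the following week means the next seven days, the repeats fall on days 15–21. All four infusions have then been given, so withdrawal spares no study drug but can still remove the primary visit. If it means the next calendar week, a Monday start puts the repeats at day 21 or later, after the visit.

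**3. Timing of the 3-month visit.** The rule has no stated end date. An abnormality confirmed at any weekly test, or at the check 3 weeks after treatment (about day 14 + 21 = 35), would remove this visit.

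**4. How many patients.** The article dates all six earlier stops to weeks 5–7. Reading that as 0 of 35 by week 3, the two-sided 95% upper limit is 1 − 0.025^(1/35) = 10.0%, and 0.100 × 26 = 2.6 patients. Hence about 0 to 3. Applying the full later rate gives 26 × 6/35 = 4.5 patients, a worst case for the primary visit.

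**5. Effect on power**, with loss in the EPO arm only (same t test, n₁ against 26):

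| EPO patients lost | n₁ | Power |
|---|---|---|
| 0 | 26 | 0.807 |
| 1 | 25 | 0.7995 |
| 2 | 24 | 0.791 |
| 3 | 23 | 0.782 |
| 4 | 22 | 0.771 |
| 5 | 21 | 0.761 |

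**6. Possible bias.** If only observed patients count, the EPO mean shifts by (share lost) × (mean of retained minus mean of lost). The documents give no value for that difference, so I assume 0.25 to 1.0 composite units. With 2 lost: 2/26 × 0.25 = 0.02 to 2/26 × 1.0 = 0.08, or 5% to 19% of 0.4. With 3 lost: 0.03 to 0.12, or 7% to 29%. For scale, the standard error of the group difference is 0.5 × √(2/26) = 0.14.

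**The case against.** The other side has a good case on size and wording.

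- **Timing.** A reader might apply the 17% directly to this trial. The documents do not support that: every one of those stops came later than this trial's primary visit, and the sponsor states that such effects are not expected with four doses. This stands, and it is why the range is 0 to 3 rather than 4 or 5.
- **Arm.** A reader might infer that losses would occur almost only under EPO. The rule applies to both arms, and no placebo rate of abnormal values is given. What can be said is that loss would probably fall mainly in the EPO arm.
- **Reticulocytes.** A reader might count both triggers as ordinary EPO effects. The article treats a reticulocyte drop as an early sign of pure red cell aplasia, with an incidence of 0.3 per 100,000 patient years, so that trigger should contribute almost no loss.
- **Intention to treat.** A reader might say that the rule contradicts the analysis. It does not. A mixed model can analyse patients as randomised with incomplete data, validly if the data are missing at random, and missing-data methods may be set out in a full protocol or SAP not shown.

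The last defence has a limit. A patient withdrawn before the second of three assessments has only a baseline value and tells the model almost nothing about change. Loss would be triggered by post-randomisation blood counts, which the analysis as described does not include. An analysis plan can set assumptions for missing outcomes; it cannot recover outcomes that were never measured.

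**Conclusion.** The point holds as an unreconciled pair of statements that invites avoidable, probably treatment-related missing data. It does not show that the primary result is compromised.

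For the primary outcome the likely effect is small: about 0 to 3 of 26 EPO patients, power 0.807 to 0.782. Even one loss takes power just under 0.8. The range rests on reading the earlier trials as having no thrombocyte stops by week 3, on loss in one arm only, and on a similar thrombocyte response here. The last is uncertain, because the first two infusions in this trial fall within about a day of each other, whereas the earlier trials dosed weekly. The bias figures rest entirely on an assumed difference between lost and retained patients.

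The 3-month follow-up, which carries the question of long-lasting benefit, is more exposed, because any confirmed abnormality before it ends participation. The documents give no rate from which to size that loss. Importance is moderate to low.

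**What to change.** Leave the safety thresholds, the repeat tests and the clinical trigger as they are. Separate stopping study medication from leaving the study, for example:

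> *A patient who stops EPO/saline for any reason remains in the trial for the planned post-treatment and 3-month assessments and is analysed in the arm to which he or she was randomised, unless consent is withdrawn.*

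The Statistical analyses section should refer to this sentence, so that the withdrawal rule and the intention-to-treat statement agree.

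The cost is a short amendment to the protocol and patient information of a trial that has been enrolling since June 2017, plus a few test sessions of about 1½ hours that were already planned for these patients. Weekly safety examinations continue after withdrawal in any case, so contact with the patient is not lost.
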